### Intervention

The group allocation protocol will be performed prior to the procedure. Based on the random number, a pre-prepared opaque envelope containing either 5% LP measuring 14 × 10 cm^2^ and containing 700 mg of lidocaine or placebo patches was allocated to the patient. There is no difference between the placebo patches and LP5 patch in appearance or structure, but the placebo does not contain lidocaine. The patch will be divided into strips and applied around the shoulder crest immediately after surgery. The patch will be replaced with a new one every 12 h until 2 weeks postoperatively. Patients, test site medical staff and investigators were blinded to group allocation. In cases of severe shoulder pain, painkillers will be allowed as emergency medication and should be documented in the medical record. Patients will also be asked to record the name, dose, date, frequency and exact time of medication used and to report to the researcher if they have taken any medication during the study. Patient compliance will be maintained and monitored through good communication and constant reminders between medical staff and patients. Although patients will be advised to adhere to the protocol, it is not possible to fully exclude those patients who independently decide to undergo and not report other treatments or measures. We will explain in detail to the patients and their family members simultaneously. A close follow-up and telemedicine will be performed during the trial.

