### Recruitment and informed consent

This study will be conducted in the First Affiliated Hospital of Soochow University. Patients with rotator cuff tears requiring arthroscopic rotator cuff repair (ARCR) will be mobilized from our outpatient centre. After confirming the patient's eligibility for inclusion and completing a baseline level assessment, the investigator will give a detailed presentation of the study protocol and potential risks, etc., and answer all the questions raised by patients and their families. Each patient will sign an informed consent form. Upon enrolment, participants will be coded with a unique number.

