### Eligibility

All patients confirmed with rotator cuff tear by MRI with symptoms (pain and/or weakness) and are failed to conservative treatments will be included. The exclusion criteria are (1) history of allergy to lidocaine or adhesive, (2) other significant organ disorders or substance abuse, (3) clear radiographic evidence of osteoarthritis of the glenohumeral joint, (4) presence of inflammatory arthritis including rheumatoid, (5) a history of ipsilateral shoulder dislocation or surgery, (6) irreparable tears, (7) pregnancy or heart disease, and (8) inability to understand questionnaires or express the level of pain.

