### Surgical procedures and postoperative rehabilitation

All ARCR procedures will be performed with the patient in the lateral decubitus position under general anaesthesia. The limb to be operated on is attached to a skin traction device and 3 kg of weight is used to keep the shoulder in a position of 30°–60° of abduction and 20°–30° of flexion. After required arthroscopic portals have been established, an arthroscopic examination will be performed, the hyperplastic bursal tissue and footprint area will be cleared, and acromioplasty will be performed based on intraoperative assessment. The tear will be repaired as clinically indicated for the tear pattern using suture anchors. All patients will receive the same postoperative rehabilitation protocol with the assistance of physical therapists.

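### Allocation precedes surgery, so a randomised patient may prove to have an excluded, irreparable tear before any patch is applied

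*Protocol article*

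**What the plan says.** All of this is in the protocol article.

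- **Allocation.** Under Intervention: "The group allocation protocol will be performed prior to the procedure". Table 1 marks allocation at baseline (time 0).
- **Eligibility.** The exclusion list contains "6) irreparable tears", with no method or time of assessment. Inclusion rests on "All patients confirmed with rotator cuff tear by MRI with symptoms (pain and/or weakness"), plus failed conservative treatment. Recruitment and informed consent puts consent "After confirming the patient's eligibility for inclusion and completing a baseline level assessment", and Table 1 puts the eligibility screen at -1 week.
- **Surgery.** "After required arthroscopic portals have been established, an arthroscopic examination will be performed". Later in the same section: "The tear will be repaired as clinically indicated for the tear pattern using suture anchors". No path is described for a tear that cannot be repaired.
- **Start of treatment.** The patch is "applied around the shoulder crest immediately after surgery".
- **After randomisation.** Withdrawal and termination criteria list the patient's own decision, loss to follow-up, and a serious adverse event or allergy. They do not list a finding at surgery. Statistical analysis names intention-to-treat as the primary analysis.

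**The concern.** The order of events is: screen, consent, allocate, look directly at the tear, repair it, apply the first patch. One exclusion criterion concerns a property of the tear that preoperative imaging may not settle, and the direct view comes after allocation. MRI is named as the way to confirm that a tear exists; nothing says how its reparability is decided.

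If a randomised patient's tear then cannot be repaired, the stated rules offer two unattractive routes. Removing the patient departs from the intention-to-treat analysis. Keeping the patient puts someone who has not had the repair into a trial of recovery after that repair, with a shoulder score at 90 days as the primary outcome. The first route loses patients and the second is likely to dilute the difference. Both could be avoided, because treatment starts only after the operation.

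**Working it through.** **Inputs.** From Sample size calculation: ASES at 3 months 63.56 (SD 15.56) in the control group and 74.94 (SD 18.42) in the intervention group; two-sided alpha 0.05; power 90%; 41 per group; 20% drop-out; 51 per group, 102 in total. The proportion *f* of randomised patients found irreparable at surgery is not in the document. I use 2%, 5% and 10% as assumptions.

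**Step 1: the plan's own figure.**

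Difference d = 74.94 − 63.56 = 11.38. Sum of variances = 15.56² + 18.42² = 242.11 + 339.30 = 581.41.

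Normal approximation: n = (1.960 + 1.282)² × 581.41 / 11.38² = 10.51 × 4.49 ≈ 47.2, so 48 per arm. The exact t calculation gives 49. The stated 41 is not reproduced with both SDs. It is reproduced if the control SD of 15.56 is used in both arms (exact t, power 90.5% at 41). That is a separate matter. Here I need only the power at 41 with both stated SDs:

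SE = √(581.41 / 41) = 3.766; noncentrality = 11.38 / 3.766 = 3.02; power (noncentral t, unequal variances) = **84.7%**.

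This 84.7%, not the stated 90%, is the reference for what follows, so that the other discrepancy is not counted here.

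**Step 2: affected patients are excluded, on top of the 20% drop-out.**

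Evaluable per arm = 51 × 0.80 × (1 − f).

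| Assumed f | Affected of 102 | Evaluable per arm | Power, n rounded down | Power, n rounded to nearest |
|---|---|---|---|---|
| 2% | 2.0 | 39.98 | 82.9% (n = 39) | 83.8% (n = 40) |
| 5% | 5.1 | 38.76 | 81.9% (n = 38) | 82.9% (n = 39) |
| 10% | 10.2 | 36.72 | 79.7% (n = 36) | 80.8% (n = 37) |

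**Step 3: affected patients are kept (intention-to-treat).**

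Assume the patch has no effect in them, the proportion is the same in both arms, and the SDs do not change. Then the difference is 11.38 × (1 − f), with 41 per arm analysed.

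| Assumed f | Diluted difference | Power at 41 per arm |
|---|---|---|
| 2% | 11.15 | 83.3% |
| 5% | 10.81 | 80.9% |
| 10% | 10.24 | 76.6% |

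**Step 4: what early allocation would cost in patients.** To keep 41 evaluable per arm when affected patients are excluded: 41 / 0.80 / (1 − f) = 52.3, 53.9 and 56.9. Rounded up, that is 53, 54 and 57 per arm, or 106, 108 and 114 in total, against the planned 102.

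**Step 5: bias.** Patients, site staff and investigators are described as blinded, and the finding is made before any patch is applied. Whether a tear is found irreparable should therefore not depend on the arm. The cost is precision or dilution.

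**The case against.** The strongest reply is that the article places eligibility before surgery: MRI confirmation, eligibility settled before consent, and a screen at -1 week. A reader might infer from the sequence that reparability is decided at arthroscopy, so that some randomised patients are certain to become ineligible. The document does not support that. It mentions the arthroscopic examination but does not say that reparability is judged there; intraoperative assessment is tied only to acromioplasty. No rate is given. This part of the objection stands, and the point can say only that patients may prove irreparable.

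A reader might also take removal after randomisation as a threat to validity. Blinding argues against that, and this part stands too.

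Third, an article can leave the handling of unrepaired patients to the full protocol or analysis plan, and the flow chart is not shown. That is fair as to the missing handling rule, which I do not count as a fault. It does not answer the timing, because the article itself fixes the allocation time, the exclusion and the start of treatment.

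Fourth, the 20% drop-out is not broken down, so it cannot be ruled out that it was meant to cover such cases. If it was, the losses in Step 2 are partly or wholly absorbed. The dilution in Step 3 is not.

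Finally, the effect is small at low rates: at 2%, about two patients and one to two points of power.

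**Conclusion.** The point holds as an avoidable design weakness. It is not a contradiction or an error. Allocation comes before the first direct view of the tear although irreparable tears are excluded and no patch is applied until after surgery, so randomised patients may prove irreparable in between.

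For illustration, at assumed rates of 2% to 10%, power falls from about 85% to between about 84% and 80% if these patients are excluded, and to between about 83% and 77% if they are kept. These figures rest on the pilot SDs applying to the primary outcome, on the assumed rates, on exclusions falling outside the 20% in the first case, and on no patch effect in unrepaired patients in the second. If preoperative screening identifies every irreparable tear, the loss is nil. No bias between arms is claimed.

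**What to change.** Keep consent and baseline assessments before surgery. Assign the next sealed, numbered patch envelope at the end of surgery, once the surgeon has confirmed that a repair was done, and define the intention-to-treat set from that point. Change Table 1 to match. Blinding is unaffected and N needs no inflation for this reason.

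The costs are modest. Envelopes must be at hand in theatre or recovery so that the patch can still go on straight after the operation. Recruitment has started, so the change must go to the ethics committee and the registry, as the protocol's own amendment section requires. The changeover date should be recorded, because patients before and after it enter the analysis set at different points.

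If the sponsor prefers to keep early allocation, the plan should state how and when irreparability is judged, say in advance how a randomised but unrepaired patient is analysed, and allow for such patients in N (106 to 114 in total at the assumed 2% to 10%, to hold 41 evaluable per arm).

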### Surgical procedures and postoperative rehabilitation

All ARCR procedures will be performed with the patient in the lateral decubitus position under general anaesthesia. The limb to be operated on is attached to a skin traction device and 3 kg of weight is used to keep the shoulder in a position of 30°–60° of abduction and 20°–30° of flexion. After required arthroscopic portals have been established, an arthroscopic examination will be performed, the hyperplastic bursal tissue and footprint area will be cleared, and acromioplasty will be performed based on intraoperative assessment. The tear will be repaired as clinically indicated for the tear pattern using suture anchors. All patients will receive the same postoperative rehabilitation protocol with the assistance of physical therapists.

### Outcomes measurement

Participants will be scheduled for a 3-month follow-up, with data collected at baseline (pre-operative), 1-, 7-, 14-, 30- and 90-day postoperative using a uniform standardized case report form. Baseline clinical data will be collected including age, gender, dominant hand, affected limb, body mass index, comorbidities, body mass index, duration of symptoms, range of motion, previous treatment to the shoulder (including surgery), and details of all treatments within the last 12 months (including the use of intra-articular therapy) (Table 1).

**Table 1 Tab1:** Schedule of study enrolment, interventions, and assessments

	Study period						
	Screening	Baseline	Treatment phase			Follow-up phase	
Timepoint	***-1 week***	***0***	***1-day***	***7-day***	***14-day***	***30-day***	***90-day***
**Enrolment**							
**Eligibility screen**	×						
**Informed consent**	×						
**Medical history**	×						
**Physical examination**	×						
**Comorbidity**							
**Allocation**		×					
**Interventions**							
**LP5 group**			×	×	×		
**Placebo group**			×	×	×		
**Outcomes**							
**ASES**		×				×	×
**OSS**		×				×	×
**CMS**		×				×	×
**ROM**		×				×	×
**SF-36**		×				×	×
**PSQI**		×	×	×	×	×	×
**VAS**		×	×	×	×	×	×
**PPT**		×	×	×	×	×	×
**Safety assessments**							
**BRE**		×					×
**URT**		×					×
**LFTs**		×					×
**ESR**		×					×
**ASO**		×					×
**RF**		×					×
**Opioid consumption**		×	×	×	×	×	×
**Adverse events**		×	×	×	×	×	×

*Abbreviations*: *LP5* 5% Lidocaine patch, *ASES* American Shoulder and Elbow Surgeons, *OSS* Oxford Shoulder Score, *CMS* Constant-Murley, *PSQI* Pittsburgh Sleep Quality Index, *SF-36* 36-Item Short Form Survey, *VAS* Visual analogue scale, *PPT* Pressure pain threshold, *BRE* Blood routine examination, *URT* Urine routine test, *LFTs* Liver function tests, *ESR* Erythrocyte sedimentation rate, *ASO* Anti-streptococcus hemolysinv, *RF* Rheumatoid factor

#### Primary outcome

The primary outcomes will be the changes from the baseline of the American Shoulder and Elbow Surgeons score (ASES) [22] at the completion of the 90-day follow-up.

#### Secondary outcome

##### Functional questionnaire assessment

Participants will complete a series of patient-reported questionnaires at the preoperative, 30-day and 90-day postoperative follow-up points to assess pain, function and patient satisfaction: Oxford Shoulder Score (OSS) [23], the Constant-Murley score (CMS) [24], Pittsburgh Sleep Quality Index (PSQI) [25] and the 36-Item Short Form Survey (SF-36) [26]. In addition to the change in ASES at the terminal follow-up, ASES at other secular nodes will also be included in the secondary outcomes. All measurements will be carried out by an independent blinded assessor.

##### Range of motion

With the patient standing, active and passive mobility of the affected and unaffected shoulder, including forward elevation (FE), external rotation (ER) and internal rotation (IR), will be recorded using a goniometer. For statistical convenience, active internal rotation of the back will be measured by recording the vertebral levels reached with the tip of the thumb. vertebral levels from T1 to T12 were numbered consecutively as 1 to 12; vertebral levels from L1 to L5 were numbered consecutively as 13 to 17 and any levels below the sacrum were numbered consecutively as 18 [27, 28].

##### Visual analogue scale

The visual analogue scale [VAS, scale from 0 (no pain) to 10 points (unbearable pain)] will be used to quantify perioperative pain at rest (VASr), pain at night (VASn) and during active movement (VASm).

##### Mechanical sensitivity

The Mechanical sensitivity will be measured with pressure pain threshold (PPT), defined as the amount of pressure applied for the pressure sensation to first transform to pain. PPT will be assessed using a 10-kgf analogic pressure algometer placed in the footprint area of the rotator cuff (Wagner Instruments, Greenwich, CT, USA). The pressure is slowly increased and the minimum value that allows the subject to report a shift to pain or discomfort is recorded. The average of three repeated measurements, with 30–60s rest intervals, will be calculated for statistical analysis [29, 30].

### Plans for collection and use of participant data and biological specimens in this trial/future use

Not applicable, as the study will not use participant data including biological specimens in the future.

### Statistical methods

#### Sample size calculation

There are no reports in the available literature relating to the primary outcome. A pre-trial with a sample size of 60 was conducted in our orthopaedic clinic. 3-month follow-up time results showed ASES scores of 63.56 ± 15.56 and 74.94 ± 18.42 in the control and intervention groups, respectively. With a type I error rate of 0.05 (*α* = 0.05, two-tail) and a power of 90% (*β* = 0.10), the sample size for the study protocol was calculated as 41 patients per group based on the primary outcome indicator by PASS 15.0 (Power Analysis and Sample Size, NCSS, LLC, USA). Assuming a 20% drop-out rate, we plan to recruit 102 participants (51 per group) to the study.

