### Randomization and blinding

Prior to the start of the study, randomization will be performed using a computer-generated table of random numbers by the research pharmacy not involved in the screening of subjects. Included participants will be randomly assigned with a 1:1 allocation to either the lidocaine or placebo group, with each patient having an equal probability of being assigned to either the experimental treatment group or the placebo group. The material, size and colour of the placebo patch will be similar to LP5 as far as possible. Patients will use the patches under the guidance of their surgeons. The group allocation protocols will be enclosed in opaque envelopes to ensure blinding of the investigators, patients, and data analysts. These envelopes will be sealed and could only be opened after the study is completed.

If a subject experiences a serious adverse event or requires emergency resuscitation during the trial, whether or not it is related to the intervention, the intervention received by the subject will be disclosed. Subjects who disclose the intervention will be considered as drop-out cases. If the intervention is disclosed for more than 20% of participants, the trial will not be considered double-blind.

In addition, the allocation scheme of the intervention will be confidential to the evaluators collecting outcome data throughout the study. The statistical analysts will also not know whether participants are in the LP5 or placebo group until the statistical analysis is completed.

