### Statistical analysis

The final data will be entered and counted by a professional statistician using SPSS 26.0 (IBM, Armonk, NY, USA). For continuous variables, the normality of measured data distributions will be evaluated using the Shapiro-Wilk test. Measurements will be expressed as mean ± standard deviation, if the data are normally distributed with uniform variance. Paired *t*-tests will be used for within-group comparisons before and after treatment, and independent samples *t*-tests will be used for between-group comparisons before and after treatment. If the data do not conform to a normal distribution or have an uneven variance, the measurement data will be expressed as median (interquartile range) [M(Q)] and the Wilcoxon rank sum test will be used for the analysis of the data before and after treatment. For categorical variables, chi-square tests or Fisher’s exact tests will be used to examine differences between groups and to describe effect sizes in terms of percentages and frequencies. Prior to any analysis, the pattern and reasons for missing data patterns will be investigated. The primary analysis will be conducted as an intention-to-treat analysis, which includes all participants with missing outcome data, unless there is clear evidence that its underlying assumption is inappropriate. Multivariable imputation by chained equations method will be used to impute missing data for the sensitivity analysis for the primary and secondary outcomes. *P*<0.05 indicates that the threshold of statistical significance has been reached.

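### The stated 41 per group for 90% power does not follow from the pilot figures printed beside it, which require 49 per group and give about 85% power at 41

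*Protocol article*

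**What the plan says.** All the planning figures stand in the protocol article under Sample size calculation. The source is an in-house pilot: "A pre-trial with a sample size of 60 was conducted in our orthopaedic clinic". It gave 3-month "ASES scores of 63.56 ± 15.56 and 74.94 ± 18.42 in the control and intervention groups, respectively". The error rate is introduced by "With a type I error rate of 0.05", specified as two-tailed, and the target power is 90%. The result is that "the sample size for the study protocol was calculated as 41 patients per group based on the primary outcome indicator by PASS 15.0". The allowance for losses follows: "Assuming a 20% drop-out rate, we plan to recruit 102 participants (51 per group) to the study".

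Three other sections bear on the check:

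- Randomization and blinding fixes equal allocation: "Included participants will be randomly assigned with a 1:1 allocation to either the lidocaine or placebo group".
- Statistical analysis names the test: "independent samples *t*-tests will be used for between-group comparisons before and after treatment". A rank-sum test replaces it if the data are non-normal or the variances unequal.
- Primary outcome defines the endpoint: "The primary outcomes will be the changes from the baseline of the American Shoulder and Elbow Surgeons score (ASES"), at the end of the 90-day follow-up.

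The article gives no other SD, no reduced planning effect, and no reason for applying one arm's SD to both arms.

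**The concern.** The section prints every input that a two-sample calculation needs, so the result should reproduce. The two SDs differ noticeably, and a required sample size rises with the sum of the two variances. A figure as low as 41 suggests that the larger SD did not enter the calculation.

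The 90% is the figure a reader will use to interpret a null result. If the printed inputs support only about 85%, the planned risk of missing the pilot effect on the 90-day score is about 15%, against the 10% claimed. A second matter limits what can be said: the SDs are those of the 3-month score, whereas the primary outcome is the change from baseline.

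**Working it through.** **Inputs** (Sample size calculation, unless noted)
- Difference: 74.94 − 63.56 = 11.38 points.
- SDs: 15.56 (control) and 18.42 (intervention).
- Two-sided alpha 0.05, power 90%, drop-out 20%.
- Equal allocation (Randomization and blinding) and an independent-samples t-test (Statistical analysis).

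**Formula.** With n per group and common SD s, the noncentrality is δ/(s√(2/n)) on 2n − 2 degrees of freedom. Power is the probability that a noncentral t variable exceeds the two-sided 5% critical value. With equal group sizes, two unequal SDs enter through their root mean square.

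**Step 1: reproduce the plan's 41.** Use s = 15.56 in both arms.
- n = 40: noncentrality 3.27, power 89.8%.
- n = 41: noncentrality 11.38/(15.56 × √(2/41)) = 3.31, power 90.5%.

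So 41 is exactly the smallest n that reaches 90%. More generally, 41 per group gives 90% only if the common SD is about 15.70 or less.

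**Step 2: use both printed SDs.** s = √((15.56² + 18.42²)/2) = 17.05, and the standardised difference is 11.38/17.05 = 0.667.

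| n per group | Noncentrality | Power |
|---|---|---|
| 40 | 2.98 | 83.8% |
| 41 | 3.02 | 84.7% |
| 48 | 3.27 | 89.9% |
| 49 | 3.30 | 90.5% |
| 51 | 3.37 | 91.6% |

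The requirement is 49 per group. Welch's test also gives 49.

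**Step 3: is the choice of formula to blame?** The normal approximation is 2 × 17.05² × (1.960 + 1.282)²/11.38² = 47.2, so 48. The arithmetic mean of the SDs (16.99) gives 47 by the normal approximation and 48 by the t-test. The intervention SD in both arms gives 57, with 78.9% power at 41. None of these comes near 41.

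Two variants do come near it, but both contradict the stated inputs. A one-sided 0.05 test with both SDs gives 39 (normal) or 40 (t). Power of 85% with both SDs gives 41 (normal) or 42 (t).

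**Step 4: drop-out.** 41/0.8 = 51.25, and the plan uses 51. This leaves 51 × 0.8 = 40.8 per group, or 81.6 in total. Reaching 49 evaluable would take 49/0.8 = 61.25, so 62 randomised per group.

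**Step 5: the change score.** The document gives neither an SD of change nor a baseline/90-day correlation r. *Assume* equal SDs of 17.05 at both times and equal baseline means. The SD of change is then 17.05 × √(2(1 − r)), and the difference in mean change is again 11.38. Power at 41 per group is:

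| r | SD of change | Power, t-test on change |
|---|---|---|
| 0.2 | 21.57 | 66% |
| 0.4 | 18.68 | 78% |
| 0.5 | 17.05 | 85% |
| 0.6 | 15.25 | 92% |
| 0.7 | 13.21 | 97% |

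For a baseline-adjusted analysis the residual SD is 17.05 × √(1 − r²). At r = 0.4 this is 15.63, and power at 41 is about 90%.

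**The case against.** The best defence is that 51 per group are randomised, and if all were analysed the power with both SDs would be 91.6%. Even 49 evaluable, a loss of about 4%, would suffice, and the article plans reminders and telemedicine to limit losses. The arithmetic is right, but it does not rescue the claim. The plan assumes 20% drop-out and presents 41 as the number sufficient for 90%.

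A second objection is that the endpoint is a change score, so the SDs of the 3-month scores are the wrong ones. This stands as a limit on the conclusion. A reader might infer that the trial's true power is 85%, or that the design cannot have 90%. The document does not support either statement for the primary endpoint. Under the assumptions of Step 5, a change-score analysis has more than 90% power at a correlation of 0.6 and less than 80% at 0.4. What the objection cannot do is make 41 follow from the figures given, since the section offers no other SD.

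A reader might also take it as established that the planners entered the control SD for both arms. That is an inference about a software run that is not shown. It fits exactly under the stated alpha and power, but the article does not say so.

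The drop-out rounding might look like a further error. It amounts to a quarter of a patient per group. Even rounding 40.8 down to 40 lowers power only from 84.7% to 83.8%, which is not material.

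Finally, the SDs and effect come from a pilot of 60 and are imprecise, and the Discussion already names the small sample as a limitation. Both are true. Neither corrects the printed power.

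**Conclusion.** The sample size statement is wrong as written. From the inputs in the article, 90% power at two-sided 0.05 needs 49 evaluable per group. The stated 41 gives 84.7%, a type II error of about 15% in place of 10%. At 41 per group, 90% power is reached only for a difference of about 12.4 points or more, against the 11.38 used for planning. The result is consistent with using the smaller SD in both arms, but the shortfall does not depend on that explanation.

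This conclusion takes the pilot means and SDs at face value and applies to an unadjusted comparison of 90-day scores with about 41 evaluable per group. Power for the actual primary outcome is unknown without an SD of change or a correlation. Only a range, under stated assumptions, can be given.

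**What to change.** Keep 102 patients and replace the power statement under Sample size calculation with one that uses both SDs and names the quantity compared, for example:

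*102 randomised, about 82 evaluable after 20% drop-out, gives about 85% power for an 11.38-point difference in 90-day ASES score (SDs 15.56 and 18.42, two-sided 0.05, unadjusted t-test).*

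Then add the power for the primary outcome itself. The pilot's SD of change is the best basis if it is available. Otherwise, give a range over an assumed baseline/90-day correlation with equal SDs: at 41 per group, about 78% at 0.4, 85% at 0.5 and 92% at 0.6. If the primary analysis were adjusted for baseline, power would be about 90% at a correlation of 0.4, and that could be stated alongside its assumption.

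The number 51 per group needs no change on account of rounding. The cost is a few sentences and a slightly less favourable stated power. No patients are added.
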